## Abstract

**Background::**

Lower extremity artery disease (LEAD) is greatly harmful to Type 2 Diabetes Mellitus patients. Traditional Chinese Medicine (TCM) is an alternative therapy to delay the development of macrovascular diseases, but the existing evidence of its efficacy, safety and mechanism of action is insufficient. We report a study protocol of a multi-center, randomized, double-blind, placebo-controlled trial that aims to use well-designed clinical trial to evaluate the efficacy and safety of Chinese herbal medicine (CHM) Shen-Qi Hua-Yu formula, and to explore efficacy mechanism of the TCM granules and the biomarkers of TCM syndrome.

**Methods::**

This is a multi-center, double-blind, randomized, and placebo-controlled study that randomized 120 participants into 2 groups. The treatment group will receive TCM granules and conventional medicine, while the control group will receive placebo in addition to conventional medicine. Two groups will receive 12-week treatment and 48-week follow-up, with a total of 13 visits. Primary efficacy outcomes included ankle brachial index. Secondary efficacy outcomes included fasting plasma glucose, blood lipid, hemorheology indexes, advanced glycation end products, the inner diameter, peak systolic velocity, end diastolic velocity and mean average velocity of the anterior tibial artery, posterior tibial artery and dorsalis pedis artery, and TCM syndrome score. The safety and endpoint outcomes will be evaluated in this trial. The study will explain the biological therapeutic mechanism of Shen-Qi Hua-Yu formula for diabetic LEAD, and try to use Isobaric tags for Relative and Absolute Quantitation (iTRAQ) and Western blot to screen biomarkers of characteristic diagnosis and clinical efficiency evaluation of the TCM syndrome.

**Discussion::**

This study is a multi-center, randomized, double-blind, placebo-controlled trial to evaluate the efficacy and safety of CHM in patients with diabetic LEAD, and to interpret the therapeutic mechanism of Shen-Qi Hua-Yu formula in treatment of diabetic LEAD through proteomics technology, and to screen biomarkers with characteristics of TCM diagnosis and clinical efficacy evaluation. On the other hand, to our knowledge, this study may be the first trial of CHM formulas to observe cardiovascular outcomes through long-term follow-up for the treatment of diabetic LEAD, which is of great value.

**Trial registration::**

This study is registered on the Chinese Clinical Trial Registry: ChiCTR1900026372.

## Introduction

1

Lower extremity artery disease (LEAD) is the major cause of foot ulcer, amputation and even death in Diabetes Mellitus patients.^[1]^ It is a risk factor of cardiovascular and cerebrovascular diseases as well. The China DIA-LEAD Study investigated 10,804 diabetic patients, and found that LEAD is the most common major vascular complication of diabetes, and the overall prevalence rate is about 21.2%.^[2]^ It imposes huge medical and economic burden to patients and the society. The basic pathological change of LEAD is atherosclerosis. Compared with patients without diabetes, LEAD in diabetic patients are characterized by more extensive affected blood vessels, more dispersed atherosclerotic lesions, more severe lumen stenosis, and more prone to plaque rupture. The degree of arterial injury in these patients is characterized by early onset, severe condition and poor prognosis.^[2,3]^

In recent years, a number of clinical studies have shown that the effect of intensive glucose control in macrovascular disease is continuing uncertainty.^[4–7]^ The cause of this phenomenon might be diabetic vascular injury attributed to various factors. Currently, the treatment of this disease needs to comprehensively evaluated and controls the risk factors that might cause LEAD injury, such as hyperglycemia, hypertension, dyslipidemia, etc. Although the clinical efficacy of statins and aspirin in the treatment of LEAD has been determined, the use of multiple drugs in combination increases the cost of medical care and tends to cause adverse reactions between drugs. The main treatment of diabetic LEAD is to control hyperglycemia, regulate dyslipidemia and stabilize atherosclerotic plaque with statins, and inhibit platelet with aspirin. The search for a comprehensive holistic approach to effectively delay or even prevent the development of new drugs for LEAD has never stopped.

In China, many patients with diabetic LEAD look for Chinese herbal medicine (CHM) formulas for treatment. In the theory of Traditional Chinese Medicine (TCM), the incidence of diabetes is fundamentally due to damage of body. The decline of body's function can produce hidden pathogenic factors such as blood stasis and continuously damage arteries. At present, this concept has been widely recognized by TCM doctors and researchers. These pathogenic factors do not have obvious manifestations in the early stage of disease. With the accumulation of pathogenic factors, the continuous abnormality of clinical indicators such as hyperglycemia and dyslipidemia eventually lead to artery injury. Blood stasis is the key pathological factor in development of diabetic LEAD. In the system of TCM, for “blood stasis” material basis research thinks, “blood stasis” contains the abnormal state of hemorheology and prethrombotic state and thrombosis, etc. It will damage the vessel wall, resulting in thickening of basilar membrane, narrowing of lumen and even blockage. CHM is divided into those that can strengthening healthy or dispel evil. Many of them have the effect of removing blood stasis. Tonifying CHM is helpful to restore the function of the body. Blood-activating and stasis-eliminating CHM is helpful to remove the stimulation of harmful factors. Therefore, it has a broad prospect to search for TCM in diabetic LEAD treatment.

Our research group has completed many national and provincial scientific research projects, a total of more than 10 studies. A large number of basic research and clinical trials prove that Shen-Qi series formulas are evidently efficient in the prevention and treatment of diabetic artery injury. We has conducted a randomized controlled trial (RCT) which is regards 120 patients with diabetic angiopathy as object (National Traditional Chinese Medicine Clinical Research Base building scientific research funding project, JDZX2012134).^[8]^ After 8 weeks of conventional hypoglycemic treatment combined with Shen-Qi series formulas in the treatment group, their TCM syndrome score, fasting plasma glucose (FPG), 2h plasma glucose (PG), and glycosylated serum protein were lower than the control group, and the life quality score was higher than that before treatment (*P* < .01), and the total effective rate was about 94.7%. We used Shen-Qi series formulas for RCT of diabetic patients (the project from the State Administration of Traditional Chinese Medicine, JDZX2015212), and after 9 months of follow-up, we found that as early as possible use of Shen-Qi series formulas in diabetic patients can be widely used to improve the whole blood viscosity, plasma viscosity, erythrocyte rigidity index, erythrocyte deformation index, erythrocyte aggregation index, fibrinogen, improve the prethrombotic state, and delay the occurrence and development of LEAD.

A meta-analysis of RCTs of Shen-Qi series formulas in the treatment of type 2 diabetic angiopathy showed that, compared with the conventional hypoglycemic agent group, Shen-Qi series formulas combined with hypoglycemic agent for the treatment of diabetic angiopathy can improve the efficiency rate, and reduce FPG, 2hPG, C-reactive protein and Leptin, as well as improve adiponectin, but it was also found that the quality of the included studies was limited.^[9]^ Therefore, it is necessary to carry out strictly designed large-scale samples, multi-center, randomized, controlled and double-blind clinical research, so as to provide high-quality evidence of evidence based medicine (EBM) for the efficacy and safety of TCM treatment of diabetic LEAD.

In the theory of TCM, the essence of diabetic LEAD is deficiency of Qi-yin and blood stasis in blood vessels. What is innovative and advantageous about this study is that it is based on syndromes differentiation of the disease. Compared with improving hyperglycemia, this approach focuses on restoring the body's own functional state.

The clinical evaluation system of the study is consists of the following five aspects: We will conduct dynamic evaluation of the efficacy of Shen-Qi Hua-Yu formula in diabetic LEAD from aspects of macrovascular protection efficacy index, endpoint event, TCM syndrome efficacy and patients’ comprehensive quality of life, and monitor the whole process of clinical intervention from the safety of TCM prescription. The study will comprehensively evaluate the intervention of Shen-Qi Hua-Yu formula in diabetic LEAD from the above 5 aspects, and establish a clinical efficacy evaluation method that reflect the characteristics of TCM prevention and treatment.

The mechanism of TCM diagnosis and treatment needs to be clarified from the aspects of symptoms, signs and material basis, especially the last one. Therefore, on the basis of EBM, the study will use Isobaric tags for Relative and Absolute Quantitation (iTRAQ), Western blot to explain the biological therapeutic mechanism of Shen-Qi Hua-Yu formula in the treatment of diabetic LEAD, and try to screen biomarkers of characteristic diagnosis and clinical efficiency evaluation of the TCM syndrome.

The purpose of this clinical study is:

(1)to evaluate whether Shen-Qi Hua-Yu formula is effective and safe for lower extremity artery lesions in diabetic LEAD patients;(2)to elucidate the biological therapeutic mechanism of Shen-Qi Hua-Yu formula for diabetic LEAD through proteomics techniques;(3)to screen biomarkers with the characteristics of TCM diagnosis and clinical efficiency evaluation.

## Methods

2

### Design

2.1

This study is a randomized, placebo-controlled, multi-center and double-blind clinical trial. The study protocol follows the recommendations of the Standard Protocol Items for Randomized Trials and the Consolidated Standards of Reporting Trials Extension for CHM Formulas statement.^[10,11]^ The study is registered on Chinese Clinical Trials.gov with approval number ChiCTR1900026372. The study will be carried out according to the following flow: First of all, screening via inclusion and exclusion criteria will lead into the run-in period; after a 4-week's run-in period, participants’ blood glucose, blood lipid and blood pressure must meet the standard before entering the treatment period; randomization; a treatment period of 12 weeks; follow-up observation will continue once every 12 weeks until 48 weeks after treatment. The research flow chart is shown in Figure 1.

**Figure 1 F1:**
[figure not shown]
Flow chart of the clinical trial.

### Study visit

2.2

In this study, participants qualified for inclusion in this trial will be selected at the first visit, and will be well-prepared for the run-in period at the second visit, at last will be randomly assigned to TCM granules or placebo at the third visit. During the treatment period, participants will receive outpatient and telephone visits every 2 weeks. At the 2nd, 6^th^, and 10th weeks of treatment, the researchers will assess the participant's response to the drug through telephone visit. At the 4th, 8th, and 12th weeks of treatment, researcher will visit participants at the research settings and be evaluated according to the research schedule. After the end of the treatment period, participants will be followed up four times at the 12th, 24th, 36th, and 48th weeks. The researchers will evaluate the changes in the outcome of lower extremity artery effective measures from baseline. Each participant will be visited 13 times in this study.

### Diagnostic criteria

2.3

#### Western medicine (WM) diagnostic criteria

2.3.1

The diagnostic criteria for diabetes is the WHO diagnostic criteria in 1999,^[12]^ and diagnostic criteria for LEAD refer to the consensus for the management of peripheral surgical disease.^[13]^ The following 2 criteria must be met simultaneously:

(1)typical diabetes symptoms and random venous PG ≥ 11.1 mmol/L or FPG ≥ 7.0 mmol/L or in an oral glucose tolerance test, 2hPG ≥ 11.1 mmol/L, or have been diagnosed as diabetes in the past;(2)conform to diagnosis of LEAD, that is, resting ankle brachial index (ABI) ≤0.90, or feel discomfort during exercise and resting ABI ≥ 0.90, such as ABI decreased by 15% −20% after bicycle ergometer test, or resting ABI < 0.40 or ankle blood pressure <50 mmHg or toe blood pressure <30 mmHg, or resting ABI > 1.3 and toe brachial index <0.65 or lower extremity vascular doppler shows abnormalities such as atherosclerotic plaque.

#### TCM diagnostic criteria

2.3.2

Referring to “Guiding principles for new drug clinical research of TCM”, the signs and symptoms of Qi-yin deficiency with blood stasis syndrome are as follows: thirst, weakness and tiredness, disinclined to talk, palpitation, insomnia, numbness or pain of limbs, legs with deep purple skin, chest distress or stabbing pain, tortuous sublingual veins, pale tongue with purple speckles with white fur, wiry and unsmooth pulse.^[14]^

### Inclusion criteria

2.4

(1)Diagnosis of LEAD of diabetes as well as Qi-yin deficiency with blood stasis syndrome according to WM and TCM.(2)According to Fontaine stage^[15]^ of LEAD, patients with stage I, II a, and II b are eligible.(3)Aged between 35 and 75 years old.(4)Glycated hemoglobin ≤9.0%.(5)Women of childbearing age are required negative pregnancy test and agree to use reliable contraception measures during the study.(6)Voluntarily participate in the test and sign the informed consent.

### Exclusion criteria

2.5

(1)Patients with cardiac and renal insufficiency, acute coronary syndrome, cerebrovascular accident, vasculitis, venous dysfunction of lower limbs, hematopoietic system disorders and mental diseases.(2)Patients with acute metabolic disorders such as diabetic ketoacidosis within the past 1 month.(3)Severe infection in the past 1 month.(4)Patients with allergic constitution.(5)Uncooperative in run-in period.(6)Having a history of alcoholism or drug abuse.(7)Having a history of another clinical study in the previous 3 months.(8)Patients considered by the investigator to be unfit for this study.

### Recruitment

2.6

There are 3 comprehensive hospitals involved in this study and participants will be recruited through posters at each participating center. The recruitment and research settings containing Hospital of Chengdu University of Traditional Chinese Medicine, Meishan Hospital of TCM, and Shuangliu area hospital of TCM. It is worth mentioning that, the primary sponsor is the Hospital of Chengdu University of TCM. It is the National TCM Clinical Research Base focusing on diabetes, the national international cooperation and exchange base of TCM, the National Clinical Trial of Chinese Medicine.

### Randomization

2.7

The randomization sequence will be generated with the PROC PLAN procedure statements of SAS software package by the statistician experts of Sichuan University, and will be concealed and disseminated using opaque envelopes.

### Blinding

2.8

In this study, researchers, participants and outcome assessors will be blinded during the trial period. Unblinding can only be performed when patient's adverse events needs to be evaluated. When an emergency occurs, the researcher should immediately inform the primary researcher. The unblinded participant will be eliminated from the study. In this study, intentional analysis will be applied to the unblinding participants. The researcher should record the reason, time and place in Case Report Forms. Statistician experts and drug management staff are not directly involved in the trial process.

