#### Endpoint outcomes

2.10.4

The endpoint incidents are defined as major adverse cardiovascular events that including cardiovascular death, myocardial infarction and ischemic stroke, or complete occlusion of the blood vessels, or ulcer, or gangrene of the lower limbs. In this study, the incidence of endpoint incident and the time of progression to endpoint incident will be selected as the indicators.

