### Statistical analysis

2.12

The statistical analysis of this study will be conducted by statisticians of the Sichuan University. They will use Statistical Analysis software packages SPSS 23.0 and SAS 9.1. Demographic and other baseline characteristics will analyze using the full analysis set (FAS). Full analysis set will analyze with intention-to-treat (ITT), and per-protocol set (PPS) will statistically analyzed. Safety analysis will be performed according to safety data set for subjects who receive at least 1 treatment after randomization. Normally distributed data is represented by mean ± standard deviation, and non-normally distributed data is represented by median and interquartile range. Comparisons between groups of measurement data will be conducted by using independent-sample *t* test, and within group differences will be tested with paired *t* test. Differences between groups of numeration data will be assessed with chi-square test. Comparison of survival rate and survival time between groups will be analyzed by Kaplan–Meier curve to explore each possible relevant factor. Covariates were then included in the multi-factor Cox regression model for analysis to detect the influence of these variables on end event of the study. This study is a multi-center clinical trial. CMH χ2 will be used for numeration data, analysis of variance (ANOVA) and an analysis of covariance (ANCOVA) will be used for measurement data, and log-rank test will be used for endpoint outcomes. After deducting the influence of polycentric effect, comparing efficacy outcomes, endpoint outcome index and safety outcomes between 2 groups.

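### Section 2.8 eliminates unblinded participants from the study yet applies an intention-to-treat analysis to them; if elimination ends assessments, later data are lost in people selected by an adverse event

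*Protocol article*

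**What the plan says.** Section 2.8 (Blinding) makes three statements that bear on this point:

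- Trigger: "Unblinding can only be performed when patient's adverse events needs to be evaluated".
- Handling: "The unblinded participant will be eliminated from the study".
- Analysis, in the sentence directly after: "In this study, intentional analysis will be applied to the unblinding participants".

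Section 2.12 (Statistical analysis) defines the sets. For efficacy: "Full analysis set will analyze with intention-to-treat (ITT), and per-protocol set (PPS) will statistically analyzed". For safety: "Safety analysis will be performed according to safety data set for subjects who receive at least 1 treatment after randomization".

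Section 2.10.1 schedules six ABI measurements: before treatment, after the 12-week treatment, and every 12 weeks during the 48-week follow-up. Section 2.10.4 adds the incidence of, and time to, endpoint incidents, defined as major adverse cardiovascular events that include "cardiovascular death, myocardial infarction and ischemic stroke, or complete occlusion of the blood vessels, or ulcer, or gangrene of the lower limbs".

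Nowhere does the article say whether an eliminated participant stops study medication, stops attending visits, or is taken out of the data set.

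**The concern.** A participant who has left the study supplies no further outcomes. An intention-to-treat analysis of that participant then has nothing to work on after the date of unblinding except what is imputed. If elimination means removal of the data, it also conflicts with a safety set that takes in everyone with at least one treatment.

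The loss is not a random thinning of the sample. The code may be opened only because an adverse event needs evaluating, so the people affected are chosen by something that happened after randomisation and may differ between the granules and placebo. For ABI this means missing values related to the participant's course. For the Kaplan-Meier, log-rank and Cox analyses it means censoring that may be related to prognosis. Section 2.8 governs data collection, so an analysis plan cannot repair it later: visits that were never made cannot be recovered by a missing-data method. With three centres and no definition of the word, sites could also apply the rule differently.

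**Working it through.** **1. The statements side by side**

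| Meaning given to elimination | Fits the intention-to-treat sentence? | Fits the safety set? | Later data collected? |
|---|---|---|---|
| Removed from the data set | No | No | No |
| Withdrawn, data to that date kept | Yes, for data to that date | Yes, for data to that date | No |
| Off study medication only, visits continue | Yes | Yes | Yes |

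Only the third meaning leaves follow-up intact, and it is the furthest from the plain sense of being eliminated from the study.

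**2. What is lost under the second meaning**

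ABI is due at baseline, at the end of treatment, and at follow-up weeks 12, 24, 36 and 48: 1 + 1 + 4 = 6. A participant unblinded during the 12-week treatment period loses the end-of-treatment value and all four follow-up values, 5 of 6. Endpoint events and safety findings after that date are lost as well. An endpoint event that came before, or prompted, the unblinding has already been observed and is counted. The exposed group for the time-to-event analysis is therefore those unblinded for an adverse event that is not itself an endpoint, because their later endpoint events go unseen.

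**3. The plan's own figure, as a check on the margin used below**

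Section 2.11 gives a difference of 0.13, a value of 0.04 that I read as a superiority margin, SDs of 0.19 and 0.11, α 0.025 and β 0.2.

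- Difference beyond the margin: 0.13 − 0.04 = 0.09.
- Common SD: √((0.19² + 0.11²)/2) = 0.155.
- With one-sided α 0.025 and 80% power, the simple two-means formula gives 47 per group. The unequal-variance noncentral t gives 48 (power 0.8006 at 48, 0.792 at 47).
- Dropout: 48/(1 − 0.20) = 60 per group, 120 in total.

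The stated 48 and 60 reproduce, which supports reading 0.04 as the margin. The present point does not alter them.

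**4. Illustration of the shift in the ABI mean (assumed inputs)**

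The article gives no unblinding rate, so u and k are assumptions. Let a fraction u of one arm be eliminated, with mean ABI lower by k than the average M over that whole arm, and none in the other arm. The mean of those remaining is (M − u(M − k))/(1 − u) = M + uk/(1 − u), so the shift is uk/(1 − u).

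| u | k = 0.05 | k = 0.10 | k = 0.19 |
|---|---|---|---|
| 2% | 0.001 | 0.002 | 0.004 |
| 5% | 0.003 | 0.005 | 0.010 |
| 10% | 0.006 | 0.011 | 0.021 |

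The largest k equals the planning SD of the treatment group. The range is about 0.001 to 0.021, against the margin of 0.04. The top of the range, roughly half the margin, needs 10% of one arm eliminated, none in the other, and a deficit of a full SD. Elimination in both arms would offset part of the shift.

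**The case against.** The strongest defence is that section 2.8 already answers the analysis question. Read charitably, an unblinded participant is withdrawn, data to that point are kept, and the person is analysed as randomised. Sections 2.8 and 2.12 can be read together that way, and an analysis plan that is not shown may set out how missing values are handled. This eases the literal contradiction. It does not restore the later assessments, so the second half of the point stands. It remains true that no sentence says outright that visits stop; the point is conditional on that, and the absence of a definition is part of the problem.

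The defence is right on several stronger readings that a reader might infer:

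- *That endpoint events or triggering adverse events disappear.* If data to unblinding are kept, an event that prompted unblinding has happened and counts. Only what comes later is lost.
- *That an emergency is a second, separate trigger.* Section 2.8 restricts unblinding to adverse-event evaluation; its emergency sentence only requires the primary researcher to be informed.
- *That the trial is underpowered as a result.* A 20% dropout allowance exists to absorb losses, and the article gives no unblinding rate that would show it exceeded.
- *That a large bias has been shown.* No event or unblinding rate is given. Treatment covers 12 of the 60 weeks, and there is less need to open the code once study treatment has ended.

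**Conclusion.** The point holds as a rule that is stated badly and should be reconciled. The conflict between the adjacent sentences of section 2.8, and between elimination and the analysis sets in section 2.12, rests on the text alone; the one interpretive step is reading the analysis sentence as intention-to-treat. The consequence is conditional: if elimination ends assessments, later ABI, later endpoint events and later safety data are missing in people selected by an adverse event, and that missingness and censoring are plausibly informative.

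The size is not established. The ABI effect is probably small if unblinding is rare: about 0.001 to 0.021 under the assumed one-arm scenarios. The effect on the time-to-event analysis cannot be put in numbers from this document. Confidence is high for the wording conflict and lower for any material bias.

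**What to change.** Replace the elimination sentence in section 2.8 with:

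> Unblinded participants remain, where they consent, in all scheduled ABI, ultrasound, endpoint and safety follow-up, and are analysed in the FAS and safety set in their randomised group with the triggering event counted; unblinding affects only PPS membership.

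In the sentence that follows, write intention-to-treat in place of the unclear term, so that it matches section 2.12. Whether study medication continues after unblinding is a clinical matter for the protocol to state separately; the replacement text leaves it open.

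The cost is a one-sentence amendment. It adds no assessments beyond those already scheduled in sections 2.1, 2.2 and 2.10, and the blinding of outcome assessors is already planned in section 2.8.
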